### Data analysis

At baseline, descriptive analyses of participants and the comparison group will assess any group differences in their characteristics (implementation or comparison), diet-sensitive condition, location site, age, military branch, and race/ethnicity. The index date for the treatment group will be the date of enrollment in the VA FCPRx program, while the index date for the comparison group will be the first date during our enrollment window in which the Veteran was listed on the eligibility roster and screened positive for food insecurity. We will construct propensity scores for program enrollment using multivariable logistic models including the independent variables listed above and use these propensity scores to conduct inverse probability treatment weighting (IPTW) analyses to compare outcomes between individuals in the FCPRx group and the comparison group. For each of these variables, our primary measure will be the value most proximal within a 2-month window surrounding the follow-up time period (i.e., 6 and 12 months). In secondary analyses, we will calculate averages for individuals with multiple values. In addition, our primary analyses will carry forward baseline values for individuals with missing values in the follow-up period. In exploratory analyses, we will include only those with non-missing outcome values.

In our primary analysis, we will assess differences in clinical measures, including body mass index (BMI), systolic blood pressure (SBP), diastolic BP (DBP), A1c, and self-reported health between patients in the treatment and comparison groups. For each outcome of interest, we will use a linear model with an ITPW approach to estimate the treatment effect and ensure the balance of baseline covariates, including baseline clinical measures. As a secondary analysis, we will compare within-person changes in clinical measures between the two groups.

Secondary outcomes include healthcare cost and utilization, and self-rated health. Exploratory outcomes include fruit and vegetable consumption, nutrition security, depression symptoms, and well-being indices. We will assess changes in secondary and exploratory outcome measures for those participants with both baseline and follow-up values. We will use generalized linear models and two-part models for healthcare cost outcomes and Poisson or negative binomial models for healthcare utilization outcomes. All comparisons will be performed at both 6- and 12-month follow-up intervals.

We will use an approach in which we will assign participants to the VA FCPRx group if they enrolled in the VA FCPRx program regardless of whether or how much of the monetary and nutrition education benefit they used over the 12-month follow-up period. In exploratory analyses, we will use a sub-analysis approach to compare enrolled patients by outcomes based on the amount of financial and educational benefit used.

Our primary analyses will consider all enrolled patients in the VA PRx group. In subgroup analyses, we will break the VA PRx patients into mutually exclusive categories based on the amount of produce purchased and adherence to the educational component of the program. For financial benefit, we will compare participants who used their card minimally, moderately, and fully. These categories will be derived based on the distribution of card use in the sample. For the educational benefit, we will compare participants who did not attend culinary education classes at all, to those who participated some of the time, to those who participated in all 4 classes. We will assess comparison group participants by reasons for non-enrollment, including not being approached for enrollment or declining to enroll. Results of these sub-analyses will inform discussions of potential selection biases and the impact on results. We may perform additional subgroup analysis, including by VHA site and other demographic differences such as race or ethnicity. Qualitative data (e.g., interview transcripts) will be analyzed using approaches including thematic analysis by an experienced qualitative team [68].

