#### Independent variables

To reduce the influence of confounding variables on our estimates, we will consider a number of measurable patient characteristics in our analyses. Demographic characteristics will include age, race, gender, marital status, priority group, insurance status, and rurality. Clinical characteristics will include the Charlson comorbidity index and the presence of mental health diagnoses. Additional information about clinical metrics and additional measures is shown in Table 2.

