### Limitations

It is important to acknowledge the limitations of VA FCPRx. Because eligibility screening data are EHR-based, we will not have results from Veterans who do not use VA care regularly. The comparison group will meet eligibility criteria but did not enroll in the program for a variety of reasons. This design choice was made to accommodate the clinical embedding approach and to offer the intervention to as many eligible Veterans experiencing food insecurity as possible during an enrollment period. However, because of the inherent differences in patients who do and do not enroll in the program, our estimated effects of the program on patient outcomes will be subject to confounding bias. Our IPTW approach should minimize the impact of measured confounders, but unmeasured confounders may still be present. Therefore, other designs (e.g., cluster randomization) may be important to examine in future work. There may be a high non-response rate for the survey, particularly in the comparison group, and all analyses will report the response rate and details of enrollment procedures. We will report characteristics of both study sites, including the number of VA nutritionists and social workers supported by the site, and we know that participating sites do not have parallel levels of support. Culinary education is offered as part of VA programming and there were no study resources assigned to this programming which may impact the effectiveness of this support. Furthermore, comparison group participants are eligible for this VA benefit and may also participate in culinary education if interested.

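### The listed propensity covariates name neither study site, qualifying condition nor baseline BMI, blood pressure and HbA1c, which does not match the balance promised for the primary weighted analysis

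*Protocol article*

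**What the plan says.** The score for program enrollment is to be built "using multivariable logistic models including the independent variables listed above" (Protocol article, Data analysis). The list itself is in the Independent variables section: "Demographic characteristics will include age, race, gender, marital status, priority group, insurance status, and rurality", and "Clinical characteristics will include the Charlson comorbidity index and the presence of mental health diagnoses". It closes with a pointer: "Additional information about clinical metrics and additional measures is shown in Table 2". Table 2 is not shown in the text at hand.

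The Data analysis section then says that each primary outcome will be analysed by a linear model with inverse probability of treatment weighting, "to estimate the treatment effect and ensure the balance of baseline covariates, including baseline clinical measures". Comparison of within-person changes is a secondary analysis. For the primary analysis, a missing follow-up value is replaced by the baseline value.

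Site and diet-sensitive condition are named among the characteristics to be described at baseline. Site returns later in Data analysis as a possible subgroup. The Limitations section states that "participating sites do not have parallel levels of support" and relies on the weighting to deal with measured confounders.

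**The concern.** Weighting by a propensity score balances the variables in the score. Others are balanced only to the extent that they are correlated with those variables. The text gives a covariate list and a balance claim, and the claim reaches further than the list. An analyst who follows the list literally would leave out each outcome's own baseline value, which is usually its strongest predictor. Site and condition would also be left out, although both are known for every Veteran on the roster.

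This matters because the study is not randomized. Veterans enter the comparison group because they were not offered the program or declined it, and the article concedes confounding. Intervention enrollment is set at 250 per site, no site split is stated for the comparison group, and the sites differ in support. Site can therefore be associated with both treatment and outcome. Carrying baseline values forward adds to the problem: where follow-up is missing, any baseline imbalance passes into the outcome in full.

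**Working it through.** **Step 1: compare the list with the claim.**

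| Variable | In the visible covariate list? | Where else in the text |
|---|---|---|
| Baseline BMI, SBP, DBP, HbA1c | Not named | Balance statement for the weighted model; carried forward if follow-up is missing; secondary change analysis |
| Study site | Not named | Baseline description; optional subgroup; Limitations |
| Diabetes, hypertension, obesity | Not named | Eligibility; baseline description |
| Prior cost and utilization | Not named | Secondary outcomes, assessed as changes |

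The balance statement covers the first row, so the list and the statement disagree there. No sentence outside Table 2 brings site or condition into the primary adjustment.

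**Step 2: the plan's own figures.** The Outcomes section gives minimal detectable differences of 0.6 for HbA1c, 6.5 for SBP, 3.5 for DBP and 2.4 for BMI. These cannot be reproduced, because alpha, power, SD and comparison-group size are not given. Assuming two-sided 0.05, 80% power and equal groups, SD = difference / (2.80 × sqrt(2/n)). For SBP this gives 6.5/0.1772 = 36.7 with 500 per group and 6.5/0.2506 = 25.9 with 250 per group. Neither setting can be confirmed, so these figures do not show whether baseline adjustment was assumed.

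**Step 3: what weighting leaves if baseline is in neither model.** This was simulated with 1,000 Veterans and 400 replicates per scenario. There were three listed covariates, one of them correlated 0.3 with baseline. Baseline SD was 1, the site odds ratio for enrollment was 1.5, and the true effect was zero. All of these are assumptions. Results for a baseline to follow-up correlation of 0.7:

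| Shift in enrollment log-odds per baseline SD | Residual baseline difference, list only (SD) | Bias, list only (SD) | Bias, baseline and site in score (SD) | Bias, list-only score with baseline as regressor (SD) |
|---|---|---|---|---|
| 0.1 | 0.09 | 0.07 | 0.00 | 0.00 |
| 0.2 | 0.18 | 0.13 | 0.01 | 0.01 |
| 0.4 | 0.35 | 0.25 | 0.00 | 0.00 |

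Site did not affect the outcome in this simulation, so the table shows the effect of baseline imbalance alone.

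**Step 4: illustration in mmHg (assumed inputs).**
- Baseline: imbalance × correlation = 3 × 0.6 = 1.8 mmHg.
- Baseline with 30% carried forward: 3 × (0.3 + 0.7 × 0.6) = 2.2 mmHg.
- Site: share difference × outcome difference between sites = (0.5 − 0.7) × 4 = −0.8 mmHg. The 0.5 follows from 250 per site; the 0.7 and the 4 mmHg are assumed.

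**Step 5: precision, with no selection on baseline.** In theory the standard error is multiplied by sqrt(1 − r²): 0.87 at r = 0.5, 0.71 at 0.7 and 0.44 at 0.9. In the simulation, adding baseline and site to the score reduced it from 0.064 to 0.056, from 0.060 to 0.045, and from 0.066 to 0.028 SD at those correlations. At 0.7, using baseline as a regressor instead gave 0.044.

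**The case against.** A reader might infer that the plan omits the baseline values, that the weighting therefore cannot achieve the stated balance, and that precision is lost. The documents do not support this. The balance statement itself names baseline clinical measures as covariates to be balanced. The list refers to a table that is not shown, and its wording need not be exhaustive. The linear model could carry the baseline value as a regressor; the text neither says so nor excludes it. Step 5 shows that either route recovers the precision.

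It is also tempting to say that staff will enroll Veterans with worse control, or that site is tied to treatment by design. No sentence says the first: offers follow a positive food-insecurity screen and presence on the roster. The second needs a site split for the comparison group, which the article does not give. The illustrative 1.8 and 0.8 mmHg are assumed and are well below the stated 6.5 mmHg detectable difference. Prior cost and utilization are partly covered, because secondary outcomes are assessed as changes. The Limitations section discloses unmeasured confounding.

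These objections settle the strength of the claim, but two things remain. The list and the balance statement do not match as written. Site and condition are measured, yet the visible text gives them no part in the primary adjustment, and the disclosed limitation concerns unmeasured confounders.

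**Conclusion.** The point holds as a mismatch that leaves the primary adjustment under-specified. Read literally, the list leaves site, qualifying condition and baseline clinical values out of the propensity score. Baseline values may well be intended; for site and condition nothing in the visible text suggests it. The size and direction of any bias are unknown. The 0.07 to 0.25 SD range depends on the assumed selection strength and a correlation of 0.7, and on baseline being in neither model. The precision loss carries the same condition. The correction is worth making before outcomes are analysed, because it concerns the main defence against confounding in a non-randomized comparison and uses variables the study already collects.

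**What to change.** Reconcile the Independent variables and Data analysis sections:

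- Add to the propensity model study site, indicators for diabetes, hypertension and obesity, and baseline BMI, SBP and DBP, with baseline HbA1c where measured. If HbA1c is available mainly in Veterans with diabetes (an assumption, since the article does not define its analysis set), check its balance within that set.
- In the weighted linear model, include site and the baseline value of the outcome as regressors alongside treatment.
- A lesser point: for cost and utilization, prior-12-month values may be added as covariates.
- Do not add calendar quarter unless the two groups overlap in calendar time. The article anticipates enrolling the comparison group after the intervention group is full. If that happens, calendar quarter would nearly determine treatment and produce extreme weights.

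The cost is a change of wording, slightly more variable weights, and some imputation of missing baseline values, for which the Data management section already plans multiple imputation of covariates.

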### VA FCPRx program

#### Produce prescription benefit

The produce prescription benefit is provided by the non-profit organization About Fresh^© ^ [42]. Enrolled Veterans receive a pre-paid card with a monthly allowance of $100 for 12 months, which can be used at participating grocery stores to purchase fresh fruits and vegetables. Each month’s prescription benefit must be used during the month of issuance and does not “roll over” into subsequent months. Participating Veterans receive a combination of live phone and text support from About Fresh for any challenges with card usage. Participating grocery stores include large, national, and locally based stores throughout Texas, Utah, and surrounding states, such as Albertson’s, Kroger/Smith’s, and Wal-Mart [43].

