### Outcome variables

#### Outcomes

Our primary outcomes will be clinical measures captured in the VA electronic health record, including BMI (constructed from height and weight values) and blood pressure readings (systolic and diastolic), which will be obtained from the Vital Status table in the VA Corporate Data Warehouse (CDW). In addition, HbA1c will be obtained from CDW laboratory data. A power analysis revealed that our planned sample will result in minimal detectable differences for HbA1c of 0.6 mmol/mol, for systolic blood pressure of 6.5 mm and 3.5 Hg for diastolic blood pressure, and 2.4 in BMI units (weight pounds x height inches) × 703).

We will construct healthcare cost variables from VA Managerial Cost Accounting datasets, which is an activity-based cost accounting system that maps VHA resource expenditures to individual patient encounters. Healthcare costs will be captured separately for outpatient, inpatient, emergency department, and pharmacy services. We will sum these costs for healthcare encounters occurring over the follow-up period and adjust for inflation to 2025 US dollars. Similarly, healthcare utilization will be calculated as the number of outpatient and emergency department visits, prescriptions, and inpatient days. These will serve as important secondary outcomes.

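### A narrow, ambiguously worded outcome window followed directly by baseline carry-forward discards real on-program readings and dilutes the primary effect

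*Protocol article*

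**What the plan says.** The Outcomes section takes BMI and blood pressure from the VA vital-sign records, and "HbA1c will be obtained from CDW laboratory data". No study visit is described for any of the three. Eligibility requires only one visit to a participating centre in the preceding 12 months.

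The Data analysis section sets these rules:
- The primary value is "the value most proximal within a 2-month window surrounding the follow-up time period", taken at months 6 and 12.
- "In secondary analyses, we will calculate averages for individuals with multiple values".
- Where the follow-up value is missing, the primary analysis carries the baseline value forward. Analysis of observed values only is exploratory.
- "The index date for the treatment group will be the date of enrollment in the VA FCPRx program".

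The Data management section also names inverse probability weighting for missing outcomes. It does not say how this combines with carry-forward.

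On the benefit itself: "Enrolled Veterans receive a pre-paid card with a monthly allowance of $100 for 12 months", and "Each month’s prescription benefit must be used during the month of issuance".

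**The concern.** Two stated rules act together. The first accepts a reading only near the target. The second replaces an empty window with baseline, with no step in between.

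Routine tests are not timed to enrollment. A Veteran with an HbA1c at month 9, after nine months of benefit, has no month-12 value on either reading of the window and is entered with zero change. The same happens to a month-10 reading if the window is 1 month either side.

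The result is shrinkage of the estimate towards no effect. There is bias as well if one group is measured more often near the target. That is possible here, because healthcare use is itself an outcome and the program includes dietitian contact.

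For blood pressure there is a further, smaller loss. One reading stands for the Veteran even when several lie in the window.

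**Working it through.** **Plan's own figures.** The article gives no expected capture or missingness. Its only computed figures are the minimal detectable differences, such as 6.5 mmHg for systolic pressure. These cannot be reproduced, because alpha, power, SD and the comparison-group size are not stated. Assuming 500 per group, two-sided 5% and 80% power, 6.5 mmHg would imply an SD of 6.5 / [(1.96 + 0.84) × √(2/500)] = 36.7 mmHg. With an assumed SD of 15 to 20 mmHg, 6.5 mmHg needs only 84 to 149 per group.

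**Capture.** Assume one test every T months, evenly spaced and unrelated to the enrollment date. The chance that a window of width w months contains a reading is min(1, w/T). The values of T are assumptions; the 500 is the planned intervention group. The last column is the expected systolic difference when the true one is 6.5 mmHg (next step).

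| T (months) | w (months) | Captured | No value, of 500 | 6.5 mmHg appears as |
|---|---|---|---|---|
| 3 | 2 | 67% | 167 | 4.3 |
| 4 | 2 | 50% | 250 | 3.25 |
| 6 | 2 | 33% | 333 | 2.2 |
| 12 | 2 | 17% | 417 | 1.1 |
| 3 | 4 | 100% | 0 | 6.5 |
| 4 | 4 | 100% | 0 | 6.5 |
| 6 | 4 | 67% | 167 | 4.3 |
| 12 | 4 | 33% | 333 | 2.2 |

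If tests instead fall at random times, capture is 1 − exp(−w/T). For T = 3, 4, 6 and 12 that gives 49%, 39%, 28% and 15% at a 2-month width, and 74%, 63%, 49% and 28% at a 4-month width.

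**Dilution.** Let p₁ and p₀ be the captured shares in the program and comparison groups, and c₁ and c₀ the true mean changes. Under carry-forward, with missingness unrelated to outcome, the expected difference in change is p₁c₁ − p₀c₀.
- Equal capture p: the true difference is multiplied by p, as in the last column.
- Unequal capture and no program effect (c₁ = c₀ = c): a spurious difference of c(p₁ − p₀) appears. For scale only, a common change of 6.5 mmHg with 67% against 50% captured gives 6.5 × (2/3 − 1/2) = 1.1 mmHg.

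**Power.** If the study has 80% power for the undiluted difference, then at p = 0.49 and fixed SD it falls to Φ(0.49 × 2.80 − 1.96) = Φ(−0.59) = 28%.

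**Blood pressure mean.** Assume a between-person SD of 12 and a visit-to-visit SD of 10 mmHg.
- One reading: √(144 + 100) = 15.6.
- Mean of 2: √(144 + 50) = 13.9, which is 11% smaller.
- Mean of 3: √(144 + 33.3) = 13.3, which is 15% smaller.

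**Time past the benefit.** A window around month 12 ends at month 13 or month 14. With uniform timing, about half of the month-12 readings fall after month 12, by at most 1 or 2 months.

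**The case against.** **Capture is not documented.** A reader might infer that many Veterans will have no usable value. The article does not support that as a fact. It gives no test frequency, and the frequency may differ between HbA1c, weight and blood pressure. An empty window also still receives an analysis value, namely baseline. The supported harm is dilution, of unknown size.

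**On the wider reading the gain is small.** If the window is already 2 months either side, a months 4 to 8 fallback adds nothing at month 6. A months 9 to 13 fallback adds only the interval from month 9 to month 10. This stands, and it is why the width must be stated first.

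**Power may have been protected.** The detectable differences may already assume far fewer than 500 analysable per group, so the fall to 28% may not apply. With an assumed SD of 18 mmHg and 500 per group, the detectable difference is 2.80 × √(2/500) × 18 = 3.2 mmHg, about the size of a half-diluted 6.5. The estimate would still be half the true effect.

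**Off-program measurement.** A reader might infer that a large part of the sample is measured off the benefit. This is a minor point. It concerns month 12 only and at most 1 to 2 months. It also depends on when the card is first loaded relative to enrollment, which is not stated. A symmetric window around the target is conventional.

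**Acute-care readings.** A reader might also infer that emergency or inpatient pressures will count. The article is silent on care setting, and an article commonly leaves such detail to the full protocol or analysis plan. No finding follows.

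**Averaging is already planned**, as a secondary analysis, and the SDs above are assumed. Averaging also helps only Veterans with several readings in the window, who are not the ones lost to an empty window. Both limits stand, so this is an improvement in precision and not the correction of an error.

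**Conclusion.** The concern holds for two stated primary rules: the outcome window, whose width has two readings, and the direct step from an empty window to baseline. Together they treat Veterans with genuine later readings as unchanged. The expected effect is multiplied by the captured share. With evenly spaced tests every 3 to 12 months, that share is 67% down to 17% at a 2-month width and 100% down to 33% at a 4-month width. These figures rest on assumed test intervals and on missingness unrelated to outcome and equal in both groups. If capture differs by group, the direction of the error is not fixed.

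Making the blood pressure mean primary is a second, smaller gain: 11% to 15% in standard error under the assumed SDs, for Veterans with 2 or 3 readings. This should be changed before analysis. It does not invalidate the design.

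**What to change.** 1. State each window in days before and after the target, and keep the value nearest the target as the rule.
2. When that window is empty, use the nearest observed value in a wider pre-specified window before any baseline value is carried forward. For example, use months 9 to 13 for the 12-month outcome and months 4 to 8 for the 6-month outcome. If the present window is 1 month either side, this raises capture from 67%, 50%, 33% and 17% to 100%, 100%, 67% and 33% under the even-spacing assumption.
3. For systolic and diastolic pressure, make the mean of eligible in-window readings primary and the single nearest reading the sensitivity analysis.
4. Keep the present window as a sensitivity analysis, and report capture by group and by outcome.

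The cost is analysis wording only, since the same EHR extract serves. There are two downsides. Some 12-month values will reflect 9 to 11 months of benefit, and the blood pressure mean is slightly less centred on the target date.

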### Data management

EHR-based demographic, health, and healthcare utilization data are stored within the VA Informatics Network Computing Infrastructure (VINCI), a secure VA computing environment. [61] Survey data from the Qualtrics survey are stored on secure University of Utah servers. Data relating to produce prescription card usage (allocated funds used per month, shopping trips per month, store locations) are transferred from Fresh Connect to the study team via a data transfer portal. Data management teams screen data for missingness and coherence of survey responses.

Three strategies will be employed to manage missing data. (1) A multiple imputation approach [62, 63] will involve creating multiple plausible imputations for missing covariate values, to maintain statistical power and reduce bias. (2) Inverse Probability Weighting [64, 65] will be used to adjust for the potential biases associated with non-random missingness in the outcome. (3) A missing indicator method [66, 67], where a binary indicator for missingness was included in the analyses, to directly account for the impact of missing categorical data on our study outcomes. These combined approaches will allow us to address different aspects of the missing data, ensuring a comprehensive analysis of the results.

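### Baseline-carried-forward is the primary handling of missing outcomes, which biases the primary estimate and leaves the planned outcome-missingness weights almost nothing to do

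*Protocol article*

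**What the plan says.** Four statements in the Protocol article bear on a missing outcome.

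- **Primary analysis (Data analysis):** "our primary analyses will carry forward baseline values for individuals with missing values in the follow-up period". No limit is set by reason, group or amount of missing data.
- **Observed values (Data analysis):** "In exploratory analyses, we will include only those with non-missing outcome values".
- **Weighting (Data management):** "Inverse Probability Weighting [64, 65] will be used to adjust for the potential biases associated with non-random missingness in the outcome". No analysis is named. Multiple imputation is described only as "creating multiple plausible imputations for missing covariate values", so it does not cover outcomes.
- **Secondary and exploratory outcomes (Data analysis):** "We will assess changes in secondary and exploratory outcome measures for those participants with both baseline and follow-up values".

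The primary clinical outcomes come from routine health-record entries, and "our primary measure will be the value most proximal within a 2-month window surrounding the follow-up time period" at 6 and 12 months. The primary model is a linear model with inverse probability of treatment weights (IPTW). Self-rated health appears in the Data analysis section both among the primary-analysis outcomes and among the secondary outcomes.

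**The concern.** A carried-forward baseline records a change of exactly zero for each unmeasured person and is then analysed as an observation. That is a strong assumption for the headline estimate. Whether a value falls in the window depends on when the Veteran attended and was measured in ordinary care. The groups are not randomised, so equal missingness cannot be taken for granted.

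The plan also names a method aimed at non-random outcome missingness but does not assign it to an analysis. Once baselines fill the gaps, the primary analysis has no missing outcome left except where the baseline is also absent, so those weights have almost nothing to act on there.

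Two things are at stake. A real effect may be understated, and a time trend shared by both groups may appear as a program effect. IPTW on baseline covariates does not by itself repair outcomes set to zero change after baseline.

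**Working it through.** **The plan's own figure.** The Outcomes section gives a minimal detectable difference of 6.5 for systolic blood pressure. It cannot be reproduced, because the article gives no alpha, power, SD or comparison-group size. Inverting the two-means formula at two-sided 5% and 80% power gives SD = 6.5 / [(1.960 + 0.842) × √(2/n)]. This is 25.9 with 250 per group and 36.7 with 500 per group. The bias below does not depend on the SD, but rejection rates do.

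**Inputs.** From the article: the carry-forward rule, the 6.5 mmHg difference and 500 intervention participants. Assumed: 500 comparators (suggested by the anticipated 1000 survey invitees), the missing shares, the common change s, a baseline to follow-up correlation of 0.6, and an SD of 18 with larger values as a check.

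**Closed form.** Take groups balanced at baseline and missingness unrelated to outcome.

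- Expected change, treated: (1−mT)(s + D)
- Expected change, comparison: (1−mC)s
- Difference: D(1−mT) + s(mC−mT)

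**Shrinkage, equal missingness, D = 6.5.** The second term is zero.

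| Missing in both groups | Expected estimate (mmHg) |
|---|---|
| 10% | 5.85 |
| 20% | 5.20 |
| 30% | 4.55 |
| 40% | 3.90 |
| 50% | 3.25 |

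**False effect, D = 0, s = −5.**

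- 20% treated and 50% comparison missing: −5 × (0.50 − 0.20) = −1.5 mmHg, an apparent benefit.
- Gap reversed: −5 × (0.20 − 0.50) = +1.5 mmHg, an apparent harm.
- 10% and 30% missing: −5 × 0.20 = −1.0 mmHg.

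**False-positive rate by simulation** (500 per group, D = 0, s = −5, 20% versus 50% missing, SD 18, nominal 5%):

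| Analysis | Rejection rate |
|---|---|
| Carry-forward, IPTW, usual robust SE | about 17% |
| Carry-forward, unadjusted | about 26% |
| Carry-forward, baseline as covariate | about 48% |
| Observed values, baseline as covariate | about 5% |

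The IPTW row is closest to the written primary model. Its SE treats the weights as known, and an SE that allowed for their estimation would reject more often.

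**Sensitivity of these rates.**

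- With s = −3 the IPTW rate is just under 5%, and the baseline-adjusted rate is 20% to 23%.
- At SD 25.9 and 36.7 with s = −5, the IPTW rates are about 6% and 2–3%, and the baseline-adjusted rates are about 27% and 16%.
- With 20% versus 30% missing at SD 18, the baseline-adjusted rate is about 10%.

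The last row of the table holds at 5% because missingness was simulated as independent of outcome.

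**The case against.** **The rules need not conflict.** A reader might infer three contradictory rules. The documents do not support that. The both-values rule covers secondary and exploratory outcomes, and carry-forward covers the primary analyses. Outcome-missingness weights are normally applied to observed cases, so they could serve the exploratory observed-value analysis and the secondary outcomes. What stands is narrower: the article does not say where the weights apply, and self-rated health falls under two rules.

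**Not every missing outcome is filled.** Carry-forward needs a baseline, so a Veteran with no baseline HbA1c still has a missing outcome on which weights could act. This is correct.

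**The scenarios are chosen, not documented.** Also correct. A reader might infer that about half of null comparisons would be declared significant. That figure needs baseline as a regression covariate, SD 18 and a 30-point missingness gap, and the article states none of these. Nor does it show that enrollees will be measured more often: comparators are active patients, screened during care and eligible for the same culinary education. How much will be missing is likewise unknown. For a test done every 6 months at a random time, a 2-month window captures 2/6 = 33% if it means ±1 month and 4/6 = 67% if ±2 months. Blood pressure comes from vital-sign records and may be taken more often.

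**Other analyses would expose the problem.** The observed-value analysis could reveal a divergence, but it is exploratory and the headline would remain the carried-forward result. The within-person change analysis gives no protection if it uses the carried-forward values.

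**Shrinkage is conservative.** This holds only with equal missingness. With unequal missingness the error can go either way.

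**Conclusion.** The point holds as a badly chosen primary rule combined with an unassigned weighting method. It is not a flat contradiction between the two sections. Under the written rule, and with missingness unrelated to outcome, the estimate is D(1−mT) + s(mC−mT): effects shrink by the missing share, and a missingness gap combined with a common trend creates a false effect in either direction. The illustrative sizes are 6.5 reduced to 3.9 mmHg at 40% missing in both groups, and −1.5 mmHg from no true effect at s = −5 with 20% versus 50% missing.

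The form of the bias is certain under those conditions. Its size in this study is not, because missingness and trends are unstated. The false-positive rate in that scenario is about 17%, 26% or 48% at SD 18, depending on the model, and is lower with a larger SD or a smaller gap. No single rate should be quoted as a property of the plan.

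**What to change.** 1. Base the primary analysis on observed follow-up values, weighted by the Data management section's outcome-missingness weights multiplied by the treatment weights, with the baseline value as a covariate. Multiple imputation of the outcome is an alternative.
2. Move baseline-carried-forward to a sensitivity analysis.
3. State one missing-data rule for self-rated health.
4. Report the share of outcomes observed by group, outcome and time point.

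This changes analysis wording only and needs no new data. It should be settled before outcomes are compared by group, so that the rule is not chosen after the results are known. The cost is somewhat wider confidence intervals and reliance on an adequate missingness model. If attendance depends on health in ways the recorded covariates miss, the weighted estimate will also be biased.
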